We plan to recruit 60 patients for the IVORY study. The sample size is based on an absolute difference of 0.2 in the primary endpoint (mean maximum target to background ratio (TBR_max_) in the index vessel) between placebo and active treatment at the end of the dosing period. This is equivalent to a 10% difference from a reference value of 2.02 and equivalent to the size effect observed after atheroprotective therapy.^35–37^ This is based on the results of previous studies that have reported less than a 10% difference in mean TBR_max_ in the index vessel between active treatment and placebo and failed to reduce cardiovascular outcomes.^34 39 41–43^

Assuming an SD of 0.24, 24 patients per arm, testing at two-sided 5% significance level, would provide 80% power. Therefore, a sample size of 30 completed patients per arm was selected to account for participant dropout and poor-quality scans deemed to be unsuitable for analysis (eg, because of motion artefact). This sample size of n=30 per group also allows the detection of a baseline-corrected 6% difference in TBRmax in the index vessel for the trial primary endpoint (mean 0.125, SD 0.166) between placebo and active treatment at the end of the treatment period, at 2-sided 5% significance level and 80% power.

The study opened on 26 August 2020. Thirty-three participants have completed the trial to date, and we expect recruitment to be completed by December 2023, after which the data analysis will commence.

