### Study protocol

The trial will be performed in accordance with the spirit and the letter of the Declaration of Helsinki, the conditions and principles of Good Clinical Practice, the protocol and applicable local regulatory requirements and law. Participants will be provided with an information sheet and given the opportunity to consider the information for at least 24 hours. They will have an opportunity during this time to discuss the study with trial staff and have any queries answered before consenting to participate in the trial. Full informed consent (online supplemental file) will be taken at the screening visit (V1) by the study team. The screening visit will also include baseline blood tests, a physical examination, vitals (blood pressure, heart rate, temperature), a clinical history and ECGs in triplicate. The screening bloods will include safety blood tests (full blood count, electrolytes/urea/creatinine, liver function tests), thyroid function tests, hsCRP, serum/urine pregnancy test where applicable and a full lipid profile.

10.1136/bmjopen-2022-062602.supp1Supplementary data

Each participant who passes screening will be assigned an ID number. The research team will complete a case record form (CRF) for each encounter with the participant. Data are then sent to the CCTU for entry into the electronic trial database. All CRFs will be stored safely, and patient identifiable information is kept confidential.

Randomisation will then be carried out using sealed envelope (www.sealedenvelope.com). Randomisation will be stratified by ST elevation status to minimise bias between the groups since patients with STEMI typically have higher circulating hsCRP levels.

During the trial, the patient facing trial team, patients and data analysis teams (immunology sample analysers and image analysers) are blinded to the treatment allocation. To maintain the overall quality and legitimacy of the clinical trial, unblinding will only occur in exceptional circumstances when knowledge of the actual treatment is essential for further clinical management of the patient.

The trial design is summarised in figure 1. After randomisation, patients will undergo an ^18^F-FDG PET/CT scan covering the ascending aorta and carotid arteries (V2).

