**Figure 4 F4:**
[figure not shown]
Analysis methods used to quantify vascular inflammation in the index vessel. TBR, target to background ratio.

Change from baseline in average TBR_max_ will be analysed using analysis of covariance, fitting treatment as a fixed effect and including baseline value and ST-elevation status as covariates. Point estimates and corresponding 95% CIs will be constructed with p-values for the relevant comparisons of interest. All nominal p-values will be reported. Multiple testing across both analyses will be controlled using a gate-keeping approach. Multiple testing corrections will be carried out to obtain the p-values.

Average mean TBR_max_ data from the final imaging visit will be plotted to show the distribution from all segments from all index vessels within each treatment group. The difference between low-dose IL-2 and placebo will be calculated and tested using a non-parametric permutation test at an individual patient level.

The number of active segments and the total number of segments will be included in logistic regression analyses to model the probability of a segment being active. For baseline correction within each group, a model will be fitted with terms for treatment and visit. For placebo and baseline correction, a model will be fitted with treatment term, including the baseline proportion of active segments as a covariate.

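### Minor: the supplementary permutation test on final-visit TBRmax has no stated baseline correction, and adding one would be a free gain in precision

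*Protocol article*

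**What the plan says.** All references are to the protocol article.

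- **Endpoint.** Table 2 and the Image analysis section define the primary endpoint as the change from baseline to follow-up in mean TBRmax of the index vessel.
- **Main analysis.** Image analysis specifies an ANCOVA of change from baseline, with treatment, baseline value and ST-elevation status in the model.
- **Permutation test.** The same section then describes a plot of averaged TBRmax values: "data from the final imaging visit will be plotted to show the distribution from all segments from all index vessels within each treatment group". The next sentence reads: "The difference between low-dose IL-2 and placebo will be calculated and tested using a non-parametric permutation test at an individual patient level". It gives no baseline term, test statistic or permutation scheme, and it does not say whether the test is confirmatory, a sensitivity analysis or descriptive.
- **Neighbouring analysis.** The logistic models for active segments, which follow directly, do state how baseline is handled.
- **Randomisation.** Under Study protocol: "Randomisation will be stratified by ST elevation status to minimise bias between the groups".
- **Sample size.** Under Study population, the first calculation takes "an absolute difference of 0.2 in the primary endpoint" and places it "between placebo and active treatment at the end of the dosing period". It continues: "Assuming an SD of 0.24, 24 patients per arm, testing at two-sided 5% significance level, would provide 80% power". The second says: "This sample size of n=30 per group also allows the detection of a baseline-corrected 6% difference in TBRmax in the index vessel", with the figures given "for the trial primary endpoint (mean 0.125, SD 0.166) between placebo and active treatment at the end of the treatment period".

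**The concern.** The only data named for the permutation test are those of the final scan. Every patient is also to be scanned before dosing, and the analyses on either side of this test state their use of baseline. A comparison of final values alone leaves in the stable differences between patients. These may be sizeable here, because the index vessel can be the aorta in one patient and a carotid in another, with blood pool measured in different veins.

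What is at stake is interpretation. The article commits to reporting nominal p-values and does not rank this test below the ANCOVA. A reader may take a permutation p-value as the assumption-light check on the primary result. If that check is much less precise than the analysis it appears to check, a non-significant permutation result beside a significant ANCOVA could be misread as fragility of the primary finding.

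**Working it through.** **1. Inputs** (Study population): difference 0.2 with SD 0.24 and 24 per arm; baseline-corrected difference 0.125 with SD 0.166 and 30 per arm; two-sided 5%, 80% power, 1:1 allocation.

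**2. Reproducing the plan's figures.** With the normal approximation, n per arm = 2(1.960 + 0.842)² × SD² / d².

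- d = 0.2, SD = 0.24: 2 × 7.85 × 0.0576 / 0.04 = 22.6, so 23. The t-test gives 23.6, so 24. Power at 24 is 80.7% (t).
- d = 0.125, SD = 0.166: 2 × 7.85 × 0.02756 / 0.015625 = 27.7, so 28. The t-test gives 28.7, so 29. Power at 30 is 81.8% (t).

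Both stated sample sizes hold.

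**3. Information lost without baseline correction.** Assume that 0.24 is the uncorrected end-of-dosing SD.

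- Variance ratio = (0.166/0.24)² = 0.478, or 2.09 the other way up.
- Share of information lost = 1 − 0.478 = 52%.
- Implied baseline to follow-up correlation = √(1 − 0.478) = 0.72 if 0.166 is an ANCOVA residual SD, or 1 − 0.478/2 = 0.76 if it is the SD of a change score.

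**4. Power for patient-level means** (noncentral t, noncentrality d / (SD × √(2/n))). For example, at n = 30 and d = 0.125 the noncentrality is 0.125 / (0.24 × 0.258) = 2.02 uncorrected and 0.125 / (0.166 × 0.258) = 2.92 corrected.

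| Difference | n per arm | Final visit, SD 0.24 | Baseline-corrected, SD 0.166 |
|---|---|---|---|
| 0.125 | 24 | 42.3% | 72.4% |
| 0.125 | 30 | 51.0% | 81.8% |
| 0.2 | 24 | 80.7% | 98.3% |
| 0.2 | 30 | 88.8% | 99.6% |

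For 80% power at 0.125 without correction, 59 per arm would be needed (t).

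**5. Simulation of the permutation test itself.** Settings: 30 per arm, 1,500 trials, 499 permutations, correlation 0.72, difference 0.125. A STEMI share of 40% and the ST-elevation effects in the table are assumptions, because the article gives neither. The adjusted version permutes residuals from a regression on baseline and ST-elevation status. Monte Carlo standard error is at most √(0.25/1500) = 1.3 points.

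| Assumed ST-elevation effect | Final visit, free | Final visit, within strata | Adjusted, free | Adjusted, within strata |
|---|---|---|---|---|
| none | 49.1% | 49.1% | 80.0% | 80.7% |
| 0.5 SD | 50.5% | 52.8% | 82.9% | 82.7% |
| 1 SD | 53.5% | 63.9% | 90.3% | 90.0% |

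With no treatment effect, free permutation of final-visit values rejected in 4.9%, 4.9% and 2.8% of trials in the three rows. It is therefore never inflated, and it is conservative when the ST-elevation effect is large.

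The gain comes almost wholly from baseline adjustment. Permuting within strata adds about 2 points to the unadjusted test at 0.5 SD and about 10 at 1 SD. It adds nothing material once the statistic is adjusted.

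**The case against.** The strongest reply is that this is a different analysis with a different purpose. The sentence follows a plot of segment-level distributions, the statistic is unspecified, and nothing says the test is meant to check the ANCOVA. The power figures above are for patient-level means, not for a comparison of segment distributions. This stands in part. It limits how literally the percentages apply, but the test is stated to be at patient level and to concern the difference between arms, so baseline information remains relevant to it.

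The magnitude also depends on how 0.24 is read. The article ties the 0.2 difference to the primary endpoint, which it defines elsewhere as a change. Only the contrast with the baseline-corrected second calculation suggests that 0.24 is a final-visit SD. This stands. If 0.24 were already the SD of a change, the article would give no final-visit SD and the loss could not be computed from it.

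A reader might also infer three stronger things, none of which the article supports:

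- **That the trial discards half its information.** It does not. The ANCOVA uses both baseline value and ST-elevation status, so any loss is confined to this added test.
- **That the permutation ignores the stratified randomisation.** The article is silent. Patient level names the unit permuted, not the scheme, and the scheme is a detail commonly left to the analysis plan, which is not shown.
- **That the test is invalid.** In a randomised trial an unadjusted final-visit comparison is unbiased on average, and the simulation shows no inflation of type I error.

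**Conclusion.** The point holds as a minor one. As described, the supplementary permutation test compares arms on final-visit TBRmax with no stated baseline correction, in a trial whose endpoint is change from baseline. At 30 per arm its power is about 51% against 82% for a difference of 0.125. At 0.2, the difference on which the sample size is based, the gap is much smaller, about 89% against 99.6%. These figures assume that 0.24 is the uncorrected end-of-dosing SD and that the test compares patient-level means. The consequence is reduced precision and a possible misreading of discordant p-values. The primary inference does not change.

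**What to change.** 1. Keep the final-visit distribution plot as a descriptive display.
2. Base the patient-level permutation test on the baseline-adjusted treatment difference, for example the ANCOVA treatment estimate recomputed for each reallocation of labels.
3. Permute labels within ST-elevation strata so that the reference distribution matches the randomisation. This completes the specification and does not correct a demonstrated error.
4. Label the test a sensitivity analysis, secondary to the ANCOVA.

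If the authors want the test only as a companion to the final-visit plot, the lesser alternative is to say so and call it descriptive.

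The cost is a sentence or two in the analysis plan and a few lines of code. No new data, visits or patients are needed, and the change should be written down before unblinding.

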Furthermore, an analysis of change from baseline in average TBR_max_ for active segments within the index vessel will be carried out, as previously described (figure 4).^35^ An active segment will be defined as a segment of a vessel with a TBR of ≥1.6. An analysis of the probability of a segment being active within the index vessel will also be calculated.

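### The active-segment logistic regression, fitted as written, ignores correlation of segments within a patient, so the standard errors of its treatment comparison are too small

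*Protocol article*

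**What the plan says.** All the relevant text is in the protocol article, Outcome measures and analysis, Image analysis.

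- Definition: "An active segment will be defined as a segment of a vessel with a TBR of ≥1.6".
- Role: "An analysis of the probability of a segment being active within the index vessel will also be calculated". Table 2 does not list this probability as a primary, secondary or exploratory endpoint.
- Response: "The number of active segments and the total number of segments will be included in logistic regression analyses".
- First model: "For baseline correction within each group, a model will be fitted with terms for treatment and visit".
- Second model, for correction by both placebo and baseline: "a model will be fitted with treatment term, including the baseline proportion of active segments as a covariate".

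No patient effect, cluster-robust variance or overdispersion term is named for either model.

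Two neighbouring analyses are specified differently. Segment data from the final scan are to be "tested using a non-parametric permutation test at an individual patient level". The ANCOVA of change in TBRmax is described as "fitting treatment as a fixed effect and including baseline value and ST-elevation status as covariates". ST-elevation status is the randomisation stratum (Study protocol section), and neither logistic model includes it.

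**The concern.** Logistic regression on a count of active segments out of a total, with no further term, takes the variance to be binomial. That is correct only if the segments of one patient are independent given the covariates. Patients were randomised, not segments.

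The measurement itself makes correlation likely. Segments come from one vessel in one patient, and the uptake values are divided by that patient's own venous blood-pool value. An error in that reference moves all of the patient's segments relative to the 1.6 cut-off together.

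If the correlation is ignored, the reported standard error of the treatment comparison is too small. The article undertakes to report all nominal p-values. A nominally significant segment result beside a null patient-level ANCOVA could then be read as support for efficacy in a 60-patient phase II trial, when it reflects only the wrong variance.

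**Working it through.** **The plan's own figures.** The article gives no figure for this analysis. Its sample size reproduces: a difference of 0.2 with SD 0.24 and 24 per arm gives 80.7% power by the t test, and 0.125 with SD 0.166 and 30 per arm gives 81.8%. Neither depends on the segment model.

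**Inputs.** From the article: 30 patients per arm, 1:1 allocation, two-sided 5%, and the terms of the two models. Assumed, because the article does not give them: segments per index vessel m = 10 to 30, within-patient ICC 0.05 to 0.3, active proportion 0.6, and between-visit correlation of patient effects 0.5 or 0.8.

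**Step 1: approximate size, treatment comparison at one visit.** The design effect is DE = 1 + (m − 1) × ICC. The reported standard error is too small by √DE, and the actual type I error is 2 × [1 − Φ(1.96/√DE)].

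| m | ICC | DE | √DE | Type I error |
|---|---|---|---|---|
| 10 | 0.05 | 1 + 9 × 0.05 = 1.45 | 1.20 | 10% |
| 20 | 0.1 | 1 + 19 × 0.1 = 2.90 | 1.70 | 25% |
| 30 | 0.3 | 1 + 29 × 0.3 = 9.70 | 3.11 | 53% |

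**Step 2: the baseline-adjusted model itself.** Adjusting for the baseline proportion removes part of the between-patient variation, so the model was simulated under no treatment effect (beta-binomial counts, 1000 trials per setting). Ranges are over the two between-visit correlations.

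| m | ICC 0.05 | ICC 0.1 | ICC 0.3 |
|---|---|---|---|
| 10 | 11% | 13–14% | 24–29% |
| 20 | 13% | 20–21% | 33–45% |
| 30 | 17–19% | 21–28% | 39–49% |

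Across these settings the standard errors are too small by a factor of about 1.2 to 2.9. Scaling the same fit by the Pearson dispersion brings type I error to 4–7%. A separate simulation with normal patient effects on the logit scale (SD 0.5 to 1.5, same m and arm size) gave about 10–51%, and about 3–6% after scaling.

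**Step 3: the visit contrast in the treatment-and-visit model.** Let ρ be the correlation of a patient's underlying effect between the two scans. A patient's mean at one visit has variance σ²[1 + (m − 1)ICC]/m, and the covariance between visits is ρ × ICC × σ². The true variance of the visit difference, divided by the binomial one, is therefore

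1 + (m − 1) × ICC − m × ρ × ICC.

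For m = 20 and ICC = 0.1 this is 2.9 − 2ρ:

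| ρ | Variance ratio | Type I error |
|---|---|---|
| 0 | 2.9 | 25% |
| 0.6 | 1.7 | 13% |
| 0.9 | 1.1 | 6% |
| 1 | 0.9 | 4% |

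The ratio falls below 1 once ρ exceeds 1 − 1/m (0.95 here). Simulation with 30 patients and m from 10 to 30 shows the same pattern: 12–52% at ρ = 0, 7–35% at 0.6, 5–13% at 0.9 and 2–5% at 1.0. Pairing the scans thus offsets the clustering, and the standard error of this contrast can be too small or slightly too large.

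**The case against.** The strongest objection is that the article is silent on variance, not wrong. It never says that segments are independent. Counts of active and total segments are also the input to quasi-binomial, beta-binomial, GEE and mixed models, and the full protocol or SAP, not shown here, may name one. This stands in part: a reader might infer that independence is declared, and it is not. But the article goes beyond naming an endpoint. It names the method and lists the terms of both models, and an analyst who follows that text literally fits a plain binomial model.

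Second, the size is assumed. Segments per vessel and ICC are not given, and a segment is not defined as one axial slice. This stands. Calling the standard errors far too small and the p-values invalid, as established fact, would go beyond the document. The direction for the treatment comparison does not depend on the inputs; with any appreciable positive ICC the type I error exceeds 5%.

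Third, the permutation test might be taken to contradict the logistic models, because it works at patient level. It does not. It is a different analysis of a different quantity, and it shows that the authors had the patient in mind as the unit.

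Fourth, one might infer that the repeated scans make matters worse throughout. For the visit contrast they do the reverse, as Step 3 shows.

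Finally, omitting ST-elevation status does not in itself make standard errors too small. It is a matter of consistency with the ANCOVA and the stratified randomisation, not part of the variance error.

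**Conclusion.** The point holds as a should-fix. As specified, the baseline-adjusted logistic model gives standard errors that are too small for the treatment comparison. Under 10 to 30 segments per vessel and an ICC of about 0.05 to 0.3, its type I error is about 10% to 50% against a nominal 5%. Those two inputs are assumptions, and an ICC near zero would leave little inflation. For the visit contrast the standard error is also not right, but the direction depends on the between-visit correlation.

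A reader might infer that the trial's efficacy conclusion is at risk. The article does not support that. The primary endpoint is one change score per patient analysed by ANCOVA, the segment distribution is tested at patient level, the sample size rests on neither logistic model, and the active-segment probability is supplementary.

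**What to change.** Keep the endpoint and the 1.6 cut-off, and state before unblinding that the patient is the unit of analysis:

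- Baseline-adjusted model: quasi-binomial (Pearson-scaled, t reference distribution) or beta-binomial, with one active/total pair per patient from the follow-up scan.
- Treatment-and-visit model: GEE or mixed logistic regression clustered on patient, with a small-sample correction, so that both the clustering of segments and the pairing of scans are handled.
- Both models: add ST-elevation status as a covariate, as in the ANCOVA.
- Take every confidence interval and p-value for this endpoint from these models.

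If the full protocol or SAP already specifies such a model, it is enough to confirm this and bring the two texts into line. The change is a sentence or two of wording and a different model option. It needs no new data and no change of design. The cost is a wider confidence interval for the treatment comparison.

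### The between-arm logistic model for active segments omits ST-elevation status, the only named randomisation stratum, although the ANCOVA beside it adjusts for it

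*Protocol article*

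**What the plan says.** All references are to the Protocol article.

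- **Study protocol section.** One stratum is named: "Randomisation will be stratified by ST elevation status to minimise bias between the groups since patients with STEMI typically have higher circulating hsCRP levels".
- **Image analysis section, ANCOVA.** Change in average TBRmax is analysed by "fitting treatment as a fixed effect and including baseline value and ST-elevation status as covariates".
- **Image analysis section, segment analysis.** The response is a count out of a total, and the event is activity of a segment: "The number of active segments and the total number of segments will be included in logistic regression analyses to model the probability of a segment". The between-arm version is described thus: "a model will be fitted with treatment term, including the baseline proportion of active segments as a covariate". ST-elevation status is not listed. No random effect, robust variance or overdispersion term is stated for the patient.
- **Same section, permutation test.** The between-arm difference is "tested using a non-parametric permutation test at an individual patient level", so the plan treats the patient as the unit there.

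A companion logistic model has terms for treatment and visit. This point concerns the between-arm model only.

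**The concern.** The two between-arm imaging models sit next to each other, both covariate lists are given, and they differ without a stated reason. The one left short is missing the factor by which patients were randomised.

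Two consequences follow in principle. First, in logistic regression, dropping a prognostic covariate moves the treatment odds ratio toward 1 even when the arms are balanced on it. Second, stratified allocation balances ST status, so it adds almost nothing to the true sampling variation of the treatment effect. A model that omits the stratum, but estimates its variance from differences between patients, still counts ST status as noise. The reported standard error is then larger than it need be, and power is lost. This would remain after within-patient clustering is dealt with.

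**Working it through.** **The plan's own figures.** The article gives no sample size, power or standard error for the segment model. Its primary-endpoint figure reproduces: n = 2(1.96 + 0.842)² × 0.24² / 0.2² = 22.6, so 23 per arm. With the t distribution it is 24, with power 0.807, as stated. That calculation is not affected here. It supplies only the trial size, 30 per arm.

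**Mechanism.** A stratum with share p and log-odds shift δ adds p(1 − p)δ² to the between-patient variance. With p = 0.5 and δ = 1.0 this is 0.25. For a patient SD of 1.2 and a baseline/follow-up correlation of 0.75, the patient variance left after baseline adjustment is 1.44 × (1 − 0.75²) = 0.63. The stratum is therefore a real but secondary part of the noise. Its effect on a grouped logistic model was found by simulation.

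**Check 1: patient-level (quasi-binomial) variance.** Assumptions, none of them in the article: half ST elevation, 20-40 segments per patient, SD 1.2, correlation 0.75, treatment log odds ratio −0.8. There were 1500 trials per setting, in two separately programmed runs, A and B. SE is the mean reported value under no treatment effect. Each pair is without/with the stratum.

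| ST shift, baseline / follow-up | SE, A | Ratio | Power %, A | SE, B | Ratio | Power %, B |
|---|---|---|---|---|---|---|
| 0 / 0 | not recorded | not recorded | 84.3 / 84.3 | 0.218 / 0.219 | 1.00 | 89.0 / 89.0 |
| 0 / 0.5 | 0.247 / 0.242 | 1.02 | 80.5 / 82.2 | 0.225 / 0.220 | 1.02 | 87.0 / 88.5 |
| 0 / 1.0 | 0.265 / 0.242 | 1.10 | 76.9 / 84.3 | 0.243 / 0.223 | 1.09 | 81.5 / 87.5 |
| 0.5 / 1.5 | 0.273 / 0.242 | 1.13 | 74.0 / 82.7 | 0.254 / 0.226 | 1.12 | 76.9 / 85.9 |

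The power loss is 1.7, 7.4 and 8.7 points in A, and 1.5, 6.0 and 9.0 in B. In B's last row the unadjusted SE (0.254) exceeds its actual sampling SD (0.226) by 12%, and the log odds ratio is −0.667 without the stratum against −0.704 with it. When ST status shifted both scans equally (by 0.5 or 1.0), power differed by under 1 point.

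**Check 2: plain binomial against patient-level variance.** Assumptions: 20 segments, patient SD 1, 40% ST elevation, ST effect at follow-up only, treatment odds ratio 0.5, 3000 trials per setting. Each pair is without/with the stratum.

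| ST odds ratio | Log odds ratio | Plain SE | Actual SD | Patient-level SE | Power %, patient-level SE |
|---|---|---|---|---|---|
| 1 | −0.624 / −0.626 | 0.124 / 0.124 | 0.214 / 0.215 | 0.218 / 0.219 | 81.3 / 81.2 |
| 2 | −0.611 / −0.626 | 0.124 / 0.125 | 0.220 / 0.224 | 0.229 / 0.219 | 75.0 / 79.3 |
| 4 | −0.577 / −0.628 | 0.123 / 0.129 | 0.212 / 0.228 | 0.259 / 0.223 | 61.3 / 79.2 |

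- *Odds ratio.* At an ST odds ratio of 4, exp(−0.577) = 0.56 without the stratum against exp(−0.628) = 0.53 with it.
- *Plain SE.* It is too small by a factor of about 1.7-1.8 (for example 0.214 / 0.124 = 1.73). Type I error at a nominal 5% is 26-28% with or without the stratum. Adding the stratum leaves the plain SE unchanged or raises it slightly.
- *Patient-level SE.* Omission raises it by 5% (0.229 / 0.219) and 16% (0.259 / 0.223), and costs 4.3 and 17.9 points of power. With patient SD 2 and an ST odds ratio of 4 the figures are 3% (0.338 / 0.328) and 6.9 points (27.8% against 34.7%). With 40 segments, SD 1 and an ST odds ratio of 4 they are 22% (0.243 / 0.200) and 18.3 points (68.3% against 86.6%).

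**The case against.** A reader might infer that the standard error of the model as written is too large and its confidence interval conservative. The documents do not support that. They describe a plain logistic regression on segment counts, and for clustered segments its standard error is too small. The excess appears clearly only with a patient-level variance, which the article does not state. With independent segments and an ST odds ratio of 4, the plain standard error did exceed its sampling SD by about 4-5% at 10 and 20 segments, but not at 40.

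Other points on that side:

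- **The ST effect is undocumented.** The article links ST status to circulating hsCRP, not to the share of active segments given the baseline share. This stands, and the size is therefore a range with zero loss at one end.
- **Part of the power gain reflects test size.** In run A the adjusted model rejected a true null about 6% of the time. Bringing it to 5% by a normal approximation (critical value 1.96 in place of 1.88) lowers its powers from 82.2, 84.3 and 82.7% to about 80, 82 and 81%. The gain at a shift of 0.5 disappears, and at 1.0 it falls from 7.4 to about 5.4 points. This stands for run A. In check 2, with 20 segments and SD 1, the adjusted patient-level test rejected 4.8-5.2% of true nulls, so the gain there is not of that kind.
- **The analysis is peripheral.** The probability of an active segment is not an endpoint in Table 2, and the ANCOVA already adjusts for ST status. This stands and sets the severity.
- **Disagreement between the two analyses proves little.** A mean difference in TBRmax and an odds ratio for exceeding 1.6 are different quantities and can differ under identical covariates. This stands, so no weight is put on it.
- **An article may condense.** The full protocol or SAP may list the stratum. But the article gives both covariate lists, so the difference is on the page.

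**Conclusion.** The point holds in limited form. The between-arm logistic model leaves out the one named randomisation stratum, while the ANCOVA includes it.

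- Omission moves the odds ratio slightly toward 1. This is a less conditional odds ratio rather than an error of estimation.
- Given a patient-level variance, and if ST status predicts follow-up activity beyond the baseline proportion, the reported standard error is about 2-13% larger and power about 1-10 points lower for assumed shifts of 0.5 to 1.5. The loss was greater in the follow-up-only settings with patient SD 1 and a strong ST effect.
- There is no material loss if ST status has no effect or the same effect at both scans.

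Segment count, patient SD, ST share and ST effect are all assumptions. Under the plain model as written, clustering dominates and the error runs in the opposite direction. Severity is minor, since the analysis is supportive. It is worth making as a free improvement.

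**What to change.** In the Image analysis section, specify the placebo- and baseline-corrected logistic model with treatment, baseline proportion of active segments, and ST-elevation status as randomised, matching the ANCOVA. State with it a variance that allows for clustering of segments within patients, such as a patient random effect, a robust variance by patient, or an overdispersed binomial. The stratum alone does not repair the standard error. If the full protocol or SAP already says this, it is enough to confirm that it does.

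The cost is one model term, one degree of freedom and one sentence on variance. No data, visits or patients are added. With patient-level variance, adding the term cost no meaningful power in any setting examined.
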